**Carbohydrate to Insulin Dose Titration Algorithm Programmed in the Insulin Pump**

| 1 hour glucose mg/dL | 3 hour glucose mg/dL | Suggested change in CHO:I ratio* | Suggested change in % bolus in first hour (relative to extended bolus)** | ROW |
|-----------------------------|-----------------------------|-----------------------------------------|---------------------------------------------------------------------------------|------------|
| <80                         | <80                         | Increase by 2                           |                                                                                 | 1          |
| <80                         | 80-180                      | Increase by 1                           |                                                                                 | 2          |
| <80                         | 181-250                     |                                         | Decrease by 10%                                                                 | 3          |
| <80                         | >250                        |                                         | Decrease by 20%                                                                 | 4          |
| 80-180               | 80-180               |                                         |                                                                                 | 5          |
| 80-180                      | 181-250                     | Decrease by 1                           |                                                                                 | 6          |
| 80-180                      | >250                        | Decrease by 2                           |                                                                                 | 7          |
| 181-250                     | <80                         |                                         | Increase by 20%                                                                 | 8          |
| 181-250                     | 80-180                      |                                         | Increase by 10%                                                                 | 9          |
| 181-250                     | 181-250                     | Decrease by 1                           |                                                                                 | 10         |
| 181-250                     | >250                        | Decrease by 2                           | Decrease by 10%                                                                 | 11         |
| >250                        | <80                         |                                         | Increase by 20%                                                                 | 12         |
| >250                        | 80-180                      |                                         | Increase by 10%                                                                 | 13         |
| >250                        | 181-250                     | Decrease by 1                           | Increase by 10%                                                                 | 14         |
| >250                        | >250                        | Decrease by 2                           |                                                                                 | 15         |

\* CHO:I ratio = grams of carbohydrate in the meal: per one unit of insulin (this ratio estimates the amount of carbohydrate in grams that are metabolized by 1 unit of insulin)

\*\* The % bolus is the amount of meal insulin delivered in the first hour after initiation of bolus administration; extended is the amount of insulin delivered in the subsequent 2-4 hours.

Columns 1 and 2 in the table indicate the glycemia at time = 1 hour (column 1) and time = 3 hours (column 2) AFTER meal ingestion. Column 3 indicates the suggested change in carbohydrate:insulin ratio (CHO:I). As can be seen from the Table, when glucose values are low, then the CHO:I ratio is suggested to be increased (see row #1 as specific example) to decrease the total amount of meal insulin delivered in subsequent meals. Contrary to the latter, the CHO:I needs to be decreased if the glucose is high (see last row for specific example). Since the process is cumulative, if the glucose levels are not corrected with an initial change in the CHO:I ratio, then it can be adjusted again when new glucose levels are available.

The distribution of the insulin bolus (as a percent distribution for the post meal period) will also be adjusted based on the finger stick at hour = 1 and hour = 3. The actual change in percentage itself will

NOT affect the total amount of insulin of the bolus, only its distribution in time. The suggested adjustments are listed in column 4 of the Table. A decrease in the percentage will result in a net decrease in the first hour and an increase in the extended period. This is the case for example in row 3 of the table. The glucose at time = 1 hour is low (less than 80 mg/dL) but is above target at time = 3 hour. By decreasing the percent bolus to 10% in the first hour, less insulin is delivered in the first hour and the same amount of insulin is shifted into the extended bolus. An example of the contrary is in row 8 where 20% increase in the percent bolus shifts insulin into the first hour (finger stick = 181-250 mg/dL) and decreases this amount in the extended bolus (since finger stick is <80 mg/dL).

There are specific combinations of glucose readings that will trigger a change in TOTAL insulin as well as in its distribution in time, for example row 11.

Some special precautions will be built into bolus administration for meals as follows:

- Assuming that gastric emptying (hence GI absorption of nutrients) may be highly unpredictable, in some patients, the insulin bolus may be delayed until the RT-CGM stream of data indicates that blood glucose has started to rise (as a proxy for GI absorption).
- The shape of the bolus will be adjusted based on the glycemic pattern observed after meals; we anticipate that we will need to use dual-wave boluses or a combination of dual-wave boluses and complementary temporary basal rates. It is safe to assume that quite a bit will be learned during the training and run-in period and that the profiles of glycemia will be highly individualized. These profiles of post-meal glucose will be identified with SMBG and compared with trends identified by adjunctive data from RT-CGM.

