**Outcome measures**

- **Primary:** The primary outcome measure is defined as the frequency and extent of mild or moderate hypoglycemic episodes (defined as a capillary glucose level less than 70 mg/dL documented by the home glucose meter and/or a reference blood glucose level if the subject is seen in a hospital (emergency room) setting and absolute number of severe hypoglycemic episodes recorded at the 12 and 24 week follow-up visits while subjects are using a combination of RT-CGM and insulin pump therapy.
- **Secondary outcome measures** will be defined to address the following:  
Effects of RT-CGM and insulin pump therapy on:
  - Hemoglobin A1c at baseline, 12, and 24 week follow-up visits

- 
- Percent time of day in hypoglycemia (<70 mg/dl), euglycemia (70-180 mg/dl), or hyperglycemia (>180 mg/dl) as determined by capillary glucose measurements and in a separate analysis by RT-CGM
  - Glycemia variability (blood glucose rate of change) based on RT-CGM readings
  - Hyperglycemia index and hypoglycemic index using capillary glucose -measurements in one analysis and RT-CGM in a separate analysis
  - Gastroparesis patient-related outcome measures using the GCSI, PAGI-SYM and -PAGI-QOL scores at baseline, 12, and 24 week follow-up visits
  - Maximal volume of water and Ensure consumed during satiety tests at baseline, 12, and 24 week follow-up visits
  - Percent tachygastria, bradygastria and normal 3 cycles per minute (cpm) activity during electrogastrogram (EGG) and satiety testing at baseline, 12, and 24 week follow-up visits
  - Vagal cholinergic and sympathetic adrenergic functions at baseline, 12, and 24 week follow-up visits

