**For Type 1 diabetes:**

1. Initial hourly basal rates will be estimated as  $(BW \times 0.2)/24$  units of insulin
2. Initial meal boluses using a carbohydrate to insulin ratio will be estimated as  $450/(BW \times 0.2)$  (grams of carbohydrate per unit insulin)
3. Initial correction factor for fasting glucose  $>110$  mg/dL, postprandial  $>140$  mg/dL will be estimated as  $1400/(BW \times 0.4)$  for capillary glucose drop per unit insulin

Alternatively, for those patients who are using a Basal-Bolus approach to control their Type 1 diabetes, the insulin pump may be programmed to use their current basal dose and carbohydrate to insulin ratios as well as correction factor.

**For those patients who are already on insulin pumps,** the insulin parameters will be adjusted based on the best prediction of needs using results from both finger stick data and baseline (run-in period) RT-CGM data.

Overall the targets for glycemia management will be:

1. Fasting glucose: 80-120 mg/dL
2. Postprandial excursions: 100-180 mg/dL

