#### 5.4 Run-in visits with insulin pump training

After successful completion of iPro (or iPro2) training, patients will return for four weekly visits, for a minimum of two weeks up to an 8-week learning period to receive training on the usage of an insulin pump coupled with RT-CGM. Participants will be trained on how to use a computer to send the data gathered by the RT-CGM, glucose meter and insulin pump to their study physician and diabetes educator. During the run-in period insulin pump infusion parameters will be adjusted to optimize regulation of blood glucose levels, using information from both their SMBG and from trend analysis of the RT-CGM which will be used only as an adjunct to SMBG.

**Run-in visit 1:** Participants will receive instruction on use of the RT-CGM, including the uploading of the data using the CareLink system as well as instructions on glycemia management using their SMBG which will be supplemented with the trend identification using the RT-CGM. The RT-CGM has a feature known as “REAL-Time Alarms” which will be set to warn patients when their glucose levels are very low or very high. The hypoglycemic alarm threshold will be set at 80 mg/dL and the hyperglycemic alarm threshold will be set at 240 mg/dL. The low glucose snooze will be set between 15-20 minutes to allow time to observe the effect of treatment for the hypoglycemia, and the high glucose snooze will be set to 1-2 hours to allow time to observe the effects of a corrective dose of insulin. They will be taught how to calibrate their RT-CGM using 2-4 glucose readings each day, obtained when there is a low rate of glucose change, as indicated by an absence of rate of change arrows. The subjects will be instructed to not make any insulin dose decisions based on the RT-CGM glucose reading without obtaining a blood glucose measurement using their glucose meter. Insulin doses may be modified based on the glucose rate of change, as was done during the JDRF and STAR 1 and STAR 3 trials. (See package insert for instructions for use of CGM)

**Run-in visit 2:** This visit should be planned within a week after the first run-in visit. Patients will be taught insulin infusion pump mechanics and will be started on an insulin pump filled with saline. The purpose of filling the pump with saline is to ensure that the patient can tolerate wearing it before it is filled with insulin.

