For adjustment of the meal boluses, an approach to adjust the total amount of insulin in the bolus by changes in the CHO:I ratio (an increase in CHO:I ratio decreases insulin dose, a decrease in CHO:I ratio increases insulin dose) will be used. The specific insulin dose titration algorithm is in the table below.

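### The meal-bolus titration table has no row for a 1-hour glucose of 80-180 followed by a 3-hour glucose below 80 mg/dL, so it prescribes nothing for that late low

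*Protocol*

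**What the plan says.** Section 5.7, under Meal Boluses, presents the table, titled "Carbohydrate to Insulin Dose Titration Algorithm Programmed in the Insulin Pump", as the operative dosing rule: "The specific insulin dose titration algorithm is in the table below". Its inputs are the glucose values 1 hour and 3 hours after a meal, each in one of four bands: <80, 80-180, 181-250 and >250 mg/dL. Its outputs are a change in the CHO:I ratio, which alters total meal insulin (a higher ratio means less insulin), and a change in the share of the bolus given in the first hour, which alters timing only. Rows are numbered 1 to 15.

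The text after the table states a general direction, "when glucose values are low, then the CHO:I ratio is suggested to be increased", and gives row 1 as its example. It also allows repeated adjustment: "Since the process is cumulative, if the glucose levels are not corrected with an initial change in the CHO:I ratio", the ratio may be changed again once new readings are available. For row 8, it explains that the change "shifts insulin into the first hour (finger stick = 181-250 mg/dL"). The same sentence goes on to give the 3-hour value below 80 as the reason for reducing the extended part.

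Elsewhere, Section 3.3 sets the target "Postprandial excursions: 100-180 mg/dL". Section 5.4 states "The hypoglycemic alarm threshold will be set at 80 mg/dL". The Design synopsis bases the primary outcome on mild or moderate episodes "defined as a capillary glucose level less than 70 mg/dL documented by the home glucose meter" or by a hospital reference value, together with severe episodes.

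**The concern.** A dosing grid should give an instruction for every cell. Here the one empty cell is a low value, in a trial whose primary outcome is hypoglycemia.

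The pattern is foreseeable. According to the table's footnote, the extended part of the bolus is delivered over the 2-4 hours after the first hour, so the 3-hour reading falls while extended insulin is being delivered or soon after. The protocol's own reason for a special algorithm is that gastric emptying in these patients may be delayed and erratic. A 3-hour value below 80 is under the postprandial target and under the low alarm, so the document itself treats it as low.

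The gap is also one-sided. For a patient in range at 1 hour, the table says how to add insulin after a late high but gives no response to a late low.

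**Working it through.** **Step 1: fill the grid.** Inputs are the 15 rows of the Section 5.7 table. CHO:I changes are in grams per unit; "share" is replaced here by *first-hour %*, meaning the portion of the bolus given in the first hour.

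| 1-hour band | 3-hour <80 | 3-hour 80-180 | 3-hour 181-250 | 3-hour >250 |
|---|---|---|---|---|
| <80 | row 1: CHO:I +2 | row 2: CHO:I +1 | row 3: first-hour % −10 | row 4: first-hour % −20 |
| 80-180 | **no row** | row 5: no change | row 6: CHO:I −1 | row 7: CHO:I −2 |
| 181-250 | row 8: first-hour % +20 | row 9: first-hour % +10 | row 10: CHO:I −1 | row 11: CHO:I −2, first-hour % −10 |
| >250 | row 12: first-hour % +20 | row 13: first-hour % +10 | row 14: CHO:I −1, first-hour % +10 | row 15: CHO:I −2 |

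4 × 4 = 16 pairs; 15 are listed and all are distinct; 16 − 15 = 1 is absent.

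**Step 2: rule out harmless explanations.** The row numbers run from 1 to 15 without a gap, and the narrative's references to rows 1, 3, 8, 11 and the last row fit that numbering, so no row was lost when the file was read. The absence is not shorthand for no change either, because no change is written out as a listed row with blank actions (row 5). Nothing else in Section 5.7 gives an action for this specific pair.

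**Step 3: can the missing entry be inferred?**

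- For a CHO:I increase: three pairs contain a low value and no high value. Two are listed (rows 1 and 2) and both raise CHO:I; the third is the missing one. The general sentence after the table points the same way. All eight rows that change timing (3, 4, 8, 9, 11, 12, 13, 14) contain a value above 180, which this pair does not.
- For a timing change: three listed rows have a 3-hour value below 80 (1, 8, 12), and two of them (8 and 12) change timing only. The explanation of row 8 ties the smaller extended part to the low 3-hour value. Rows 3, 4, 8 and 12 each contain a low value yet leave CHO:I alone, so the general sentence is not applied without exception.

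The balance favours a CHO:I increase but does not settle it. The step is not settled either: row 1 uses 2 and row 2 uses 1.

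**Step 4: size of the candidate instruction.** Bolus = meal carbohydrate ÷ CHO:I. For the protocol's own 90-gram example:

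- At CHO:I 10: 90/10 = 9.00 units. A step of 1 gives 90/11 = 8.18 (−9.1%); a step of 2 gives 90/12 = 7.50 (−16.7%).
- At CHO:I 30: 90/30 = 3.00 units. A step of 1 gives 90/31 = 2.90 (−3.2%); a step of 2 gives 90/32 = 2.81 (−6.25%).
- A timing-only entry leaves the total unchanged.

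These figures describe how large an adjustment goes unwritten. They do not measure harm.

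**The case against.** The strongest reply is that staff are not left without direction. Section 5.7 calls the rules guidelines, and both action columns are headed as suggested changes. Staff review glucose weekly (Section 5.6), bolus shape is individualised to the pattern seen after meals (Section 5.7), adjustment is cumulative, and acute lows are treated under Section 6.2. The <80 band also takes in values of 70-79 that are not outcome events. All of this stands and limits the practical effect. It does not supply the row: a late low is left to each site's judgment, while the matching late highs are not.

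Three stronger readings are tempting, and the document does not support them.

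- A reader might infer from the table's title that the pump titrates automatically and would skip this pair. Section 5.7 describes only a pump that computes a bolus from the entered ratio and delivers it if the patient accepts.
- A reader might infer that the missing entry must be a cut in total insulin. The row 8 explanation prevents that: it links a low 3-hour value to less extended insulin, so a timing change cannot be strictly excluded.
- A reader might take the percentages above as excess hypoglycemia. They are the size of a hypothetical step; the document gives neither the frequency of the pair nor any link to the event rate.

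**Conclusion.** The point holds as an omission: 1 of 16 glucose-band pairs has no instruction, and it is 1 of the 3 pairs with a low and no high value. Followed literally, the algorithm adds insulin for a late high after an in-range 1-hour value and does nothing for the corresponding late low. That should be corrected in a trial with a hypoglycemia primary outcome.

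The finding that a row is missing rests on the table alone and needs no outside assumption. What the row should say is a clinical judgment that the document informs but does not fix. The practical effect is limited, and its size on the event rate is unknown. The outcome definition, sample size and analysis are not touched.

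**What to change.** Add a row for 1-hour 80-180 with 3-hour <80. The proposed default is an increase of 1 in CHO:I and a blank timing column. This is the counterpart of row 2 (one low and one in-range value) and the mirror of row 6 (in range at 1 hour, one band high at 3 hours). The study diabetologists should confirm the entry or replace it with a timing change or a different step. Then reissue the table to all seven centers.

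The cost is one table row in a protocol amendment and a site memo, with no added visits, procedures or patients.

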**For Type 2 diabetes:**

1. Initial hourly basal insulin rate will be estimated as  $(BW \times 0.4)/24$  units of insulin
2. The initial carbohydrate to insulin ratio for meal boluses will be estimated as  $450/(BW \times 0.84)$  (grams of carbohydrate per unit insulin)
3. Initial correction factor for fasting glycemia  $>110$  mg/dL, postprandial  $>140$  mg/dL will be estimated as  $1700/(BW \times 0.8)$  for capillary glucose drop per unit insulin

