### 5.6 Follow-up visits

Patients will return for follow-up visits, once every 4 weeks over a 24-week period after enrollment. During these visits, patients will meet with the diabetes educator and have their insulin pump parameters (basal rate, carbohydrate to insulin ratio for meals, etc.) adjusted according to their SMBG and trends observed from the RT-CGM.

The blood glucose measurements of patients will be reviewed by the study staff on a weekly basis using the CareLink system and suggestions for insulin pump adjustments will be provided to the patient via the phone or during a study visit. In addition, symptoms of gastroparesis will be managed according to the prevailing standard of care including appropriate use of antiemetic and prokinetic medications as outlined in SOP IV: Standard of Care for Patients with Diabetic Gastroparesis.

**Week 4 visit:** Patients will meet with a diabetes educator to review blood glucose levels and to make necessary adjustments to insulin doses through the insulin pump. The Follow-up Medical History form will be completed. Any unanticipated adverse events will be reviewed with the patient and recorded on case report forms.

**Week 8 visit:** Patients will meet with a diabetes educator to review blood glucose levels and to make necessary adjustments to insulin administration by adjustment of parameters of the pump. The Follow-up Medical History form will be completed. Any unanticipated adverse events will be reviewed with the patient and recorded on case report forms.

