#### Meal Boluses

The adjustment for meal related glycemia is of special interest in the GLUMIT-DG study since gastric emptying may be erratic and delayed. For the GLUMIT-DG study, the following guidelines will be used for adjustment of meal boluses at all subsequent follow-up visits or phone contacts.

Insulin administered for meal(s) will be tailored using a dual wave pattern. The amount of insulin for the specific meal will be estimated using the carbohydrate to insulin ratio (CHO:I). This ratio is the estimated amount of meal carbohydrate that one unit of insulin metabolizes. This ratio is calculated initially by the following formulas (see also Section 3.3):

(1)  $450/(\text{BW (kg)} \times 0.84)$  for Type 2 diabetes, and

(2)  $450/(\text{BW (kg)})$  for Type 1 diabetes

The carbohydrate to insulin ratio is in the following units: grams of meal carbohydrate for every unit of insulin. The ratio is entered into the insulin pump. When the patient is about to eat or has already eaten, he/she enters into the pump the estimated amount of carbohydrate ingested during the meal or the meal the patient is preparing to eat. The microchip in the pump uses the pre-entered CHO:I ratio to calculate the bolus of insulin to be delivered. For example, if the meal carbohydrate is calculated as 90 grams and the CHO:I ratio is 30, then the pump will calculate a total of 3 units of insulin. If the same amount of meal carbohydrate is eaten and the CHO:I ratio is 10, then the total amount of meal insulin calculated is 9 units. Thus a higher CHO:I ratio yields a lower calculated insulin bolus and vice versa. The pump will prompt the user to confirm acceptance of the suggested dose and will not deliver the bolus unless the patient accepts the suggestion from the pump.

The bolus of insulin can be delivered in TOTAL during a short period of time (standard bolus) or it can be

delivered over a prolonged period of time (extended or square wave bolus). A dual wave bolus can be configured by delivering a certain % of the dose immediately (standard bolus) and the rest over several hours after meal ingestion (extended square wave bolus). These times can be tailored as per the judgment of the diabetologist and diabetes educator. For obvious reasons, the second approach is better suited for patients with gastroparesis since it diminishes the possibility of hypoglycemia and will be used in the GLUMIT-DG study.

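### The section 5.7 meal-bolus table moves the carbohydrate-to-insulin ratio by a fixed 1 or 2 g/unit, so the same entry raises doses by 7% at a ratio of 30 and by about 60% at a type 2 starting ratio for an assumed 100 kg

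*Protocol*

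**What the plan says.** Section 5.7 (Meal Boluses) introduces the rule with "The specific insulin dose titration algorithm is in the table below". Rows of the table are selected by the 1-hour and 3-hour glucose bands. The third column, headed "Suggested change in CHO:I ratio", holds only four entries: up 2, up 1, down 1 or down 2. The decrease of 2 is in rows 7, 11 and 15, all with 3-hour glucose above 250 mg/dL. Row 4 also has a 3-hour value above 250 but leaves the ratio alone. The notes below the table explain that "the CHO:I needs to be decreased if the glucose is high (see last row for specific example", and describe the process as cumulative.

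The ratio is defined in grams of carbohydrate per unit of insulin. The worked example starts "if the meal carbohydrate is calculated as 90 grams and the CHO:I ratio is 30" and arrives at 3 units; at a ratio of 10 the same meal needs 9 units. For type 2 patients new to a pump, section 3.3 says "The initial carbohydrate to insulin ratio for meal boluses will be estimated as" 450/(BW x 0.84), with BW in kilograms. Section 5.7 repeats that formula.

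**The concern.** The dose is inversely proportional to the ratio, so a fixed subtraction is a small change when the ratio is large and a large one when it is small. Nothing in the table, its notes or section 3.3 scales the step to the current ratio, limits the resulting dose change or sets a lowest permitted ratio. Two patients in the same table row can therefore receive very different increases in insulin from the same entry.

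The largest increases fall on patients with the lowest ratios. By the section 3.3 formula these include heavier type 2 patients, and type 2 patients make up 20 of the planned 40. Hypoglycaemic episodes are the primary safety outcome (section 8.2), and section 5.7 itself notes that gastric emptying in these patients may be erratic and delayed. At high ratios the weakness runs the other way: the entry does little for a patient who is still above 250 mg/dL.

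**Working it through.** **Inputs.** Dose relation, example meal (90 g) and example ratios (30 and 10): section 5.7. Step sizes: section 5.7 table. Type 2 starting ratio: section 3.3. Body weight is an assumption, because the protocol gives no weights; 60 to 130 kg is shown.

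**Protocol figures reproduced.** Dose = carbohydrate / ratio. 90/30 = 3 units and 90/10 = 9 units, as stated.

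**Formula.** With current ratio R, lowering it by d multiplies each later meal dose by R/(R - d); raising it by d multiplies the dose by R/(R + d). Meal size cancels.

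**One decrease of 2, on a 90 g meal**

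| Ratio R | Source | R/(R - 2) | Change | Dose (units) |
|---|---|---|---|---|
| 30 | protocol example | 30/28 = 1.071 | +7% | 3.00 to 3.21 |
| 10 | protocol example | 10/8 = 1.250 | +25% | 9.00 to 11.25 |
| 5.36 | type 2 start, 100 kg: 450/84 | 5.357/3.357 = 1.596 | +60% | 16.8 to 26.8 |

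**Type 2 starting ratio by assumed weight, one decrease of 2**

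| Weight (kg) | 450/(0.84 x BW) | Change |
|---|---|---|
| 60 | 8.93 | +28.9% |
| 70 | 7.65 | +35.4% |
| 80 | 6.70 | +42.6% |
| 100 | 5.36 | +59.6% |
| 120 | 4.46 | +81.2% |
| 130 | 4.12 | +94.3% |

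**Other entries, at ratios 30, 10 and 5.36.** A decrease of 1 gives +3.4%, +11.1% and +23.0%. An increase of 2 (row 1) gives -6.2%, -16.7% and -27.2%.

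**Two decreases of 2 in succession.** At 30: 30/26 = 1.15. At 10: 10/6 = 1.67. At 5.36: 5.357/1.357 = 3.95, made up of 1.596 for the first step and 3.357/1.357 = 2.474 for the second. The second step is proportionally larger than the first.

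Type 1 starting ratios are not used here because sections 3.3 and 5.7 give different formulas for them, 450/(BW x 0.2) and 450/BW. That is a separate matter.

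**The case against.** The strongest reply is that the table does not act alone. Its steps are suggestions within guidelines, applied at visits or phone contacts. Section 5.6 says "The blood glucose measurements of patients will be reviewed by the study staff on a weekly basis". The patient must accept each bolus, the low-glucose alarm is set at 80 mg/dL (section 5.4), and pump settings are adjusted during the run-in, so formula ratios need not persist. One row 1 step exactly reverses one decrease of 2. All of this stands, and it limits the harm. None of it scales the step, and the table gives staff at seven centres no signal that one entry can mean 7% or 60%.

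A reader might infer more: that one step would drive a heavy type 2 patient into hypoglycaemia. The protocol does not support that. Such a forecast applies the type 2 starting correction factor in section 3.3, 1700/(BW x 0.8), which is 21.25 mg/dL per unit at 100 kg. The answer then turns on meal size. On 90 g the extra 10.01 units imply a fall of 10.01 x 21.25 = 213 mg/dL. On 60 g the extra 60/3.357 - 60/5.357 = 6.67 units imply 142 mg/dL, which takes 251 to 109, inside the stated target ("Postprandial excursions: 100-180 mg/dL"). The forecast also takes the lowest glucose that triggers the row and an assumed weight. It uses a starting sensitivity for someone who, being still above 250, may be less sensitive to insulin. It further treats insulin action as complete at 3 hours, although part of the bolus is delivered over the following 2 to 4 hours.

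Nor is this an arithmetic error: every figure the protocol states here reproduces.

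**Conclusion.** The point holds as a design weakness in a dosing rule. Followed as written, one table entry changes later meal doses by 7% to 25% at the protocol's own example ratios, and by 29% to 94% at type 2 starting ratios for assumed weights of 60 to 130 kg. The first pair of figures needs no assumption beyond the protocol's dose relation. The second rests on assumed weights and on a patient still at the formula's starting ratio. The 3.9-fold figure for two steps at 100 kg shows that the text sets no limit; it does not forecast that staff would let this happen. Because the steps are advisory and glucose is reviewed weekly, a correction is advisable but the trial does not depend on it.

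**What to change.** In the third column of the section 5.7 table, keep the present steps at higher ratios and use smaller ones at low ratios, either by bands of current ratio or as a percentage of it. Add one sentence setting a maximum percentage dose increase per step, above which the diabetologist must decide. The study diabetologists should set the bands and the limit.

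The cost is one revised table column, one added sentence and a short retraining note. The table becomes slightly less simple, and high glucose will be corrected more slowly in some patients with low ratios.
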